### Secondary outcomes

Secondary outcomes will include the PEG score at 6 and 12 months, physical functioning, QOL (WHO QOL 2 items; CDE measure), sleep (PROMIS short form sleep disturbance and sleep-related impairment forms), depression (PHQ-8), anxiety (GAD-7), and global satisfaction with treatment (Patient Global Impression of Change) [80–86]. Secondary outcomes will be measured at baseline, 3, 6, and 12 months. Global satisfaction will be measured at 6 and 12 months.

#### Mediators and common factors

Primary mediators (i.e., variables most directly linking the intervention with desired outcomes) will be assessed at timepoints listed in Table 1 and will include pain cognitions (catastrophizing, psychological flexibility, pain self-efficacy) and health behavior (behavioral activation, exercise, movement, sleep) [88–91]. Secondary mediators (i.e., variables that indirectly exert influence on outcomes) include stigma and isolation, trust in healthcare, engagement, and satisfaction with the INSPIRE intervention [92–95]. The hypothesized INSPIRE Treatment Effects Pathway Model is described in Fig. 3.

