## Methods

### Trial design

The efficacy of the INSPIRE intervention will be determined by a multisite, parallel, two-arm pragmatic RCT comparing intervention participants with waitlist controls over a study period of 12 months. The primary outcome will be PEG scores at 3 months with secondary outcomes including PEG at 6 and 12 months, and physical functioning/quality of life, sleep, depression, anxiety, and global satisfaction with treatment at 3, 6, and 12 months. Secondary analyses will also determine if primary mediators of pain cognitions (catastrophizing, psychological flexibility, pain self-efficacy) and health behavior (behavioral activation, exercise, movement) and secondary mediators of stigma and isolation, trust in healthcare, and satisfaction with the INSPIRE intervention play a role in improved pain outcomes.

The feasibility and acceptance (F&A) of this research protocol was first assessed in a 3-month, single-arm pilot of *n*=24 participants (8 from each language group). F&A outcomes included the success of participant recruitment and retention, patient adherence, intervention fidelity, data collection tools and schedule, and participant satisfaction. Feedback on the trial methodology and the mobile app was collected and used for optimization prior to the start of the RCT. The study protocol is summarized in the flowchart (Fig. 1). The Study protocol adheres to the Standard Protocol Items: Recommendations for Interventional Trials (SPIRIT) 2025 guidelines [79]. The SPIRIT Checklist can be found in Additional file 2, and the “SPIRIT Figure” study timeline can be found in Table 1.

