**ASSESSMENTS**							
Primary Outcome							
PEG [80]		X	X		X		X
Secondary outcomes							
Quality of life (WHOQOL)		X					X
PROMIS Physical functioning 6b [81]		X	X		X		X
PROMIS Sleep Disturbance 6a [82]		X	X		X		X
Sleep duration [83]		X	X		X		X
PHQ-8 (Depression) [84]		X	X		X		X
GAD-7 (Anxiety) [85]		X	X		X		X
Global Impression of Change [86]			X				X
TAPS-1 & TAPS-2 (Substance Use) [87]		X	X		X		X
Primary Mediators							
Pain Catastrophizing [88]		X	X		X		X
Psychological Inflexibility [89]		X	X		X		X
Pain Self-Efficacy [90]		X	X		X		X
Behavioral/Social activation [91]		X	X		X		X
Secondary Mediators							
PROMIS Social isolation 8a [92]		X					X
Internalized Stigma [93]		X					X
Healthcare Relationship Trust [94]		X					X
Adherence/Engagement			X				X
Mobile App Rating Scale [95]			X				
Other Covariates							
Demographics		X					
Digital Health Literacy [96]		X					

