## Outcomes and study measures

### Study measures

Participants will be asked to complete surveys at baseline and at 3, 6, and 12 months. Measures were selected based on the HEAL Common Data Elements and our hypothesized INSPIRE treatment effects pathway model (Fig. 3) [83]. Instruments were translated to Spanish and Chinese (traditional) when necessary and validated when possible. All published measures are cited in Table 1. Adherence with the INSPIRE intervention will be measured with app usage data including module completion rates and log in times, and attendance for coaching sessions. We will collect demographic information including age (in years), race, ethnicity, level of education, employment status, and annual household income as noted in Additional file 4. Other characteristics will include disability insurance, rural-urban commuting area code, and duration of pain.

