### Causal mediation analysis

Although the ITT analysis will provide the estimated overall effect of INSPIRE on PEG scores, we will conduct a secondary analysis to understand the pathways of effect for INSPIRE to improve PEG scores around or through intermediate variables using mediation analyses [123–125]. Specifically, a generalized linear model will be fitted for mediators at follow-ups as the outcome and the intervention (INSPIRE vs. control) as the predictor, and then another linear model will be fitted for the outcome PEG reduction over 12 months on the intervention (INSPIRE), mediators, and intervention*mediator interactions with relevant baseline covariates included in the models. Based on the quasi-Bayesian Monte Carlo approximation, estimates from the models will be used to compute the direct and indirect (mediation) effects of the intervention around and through the mediators on CP management [126]. A significant mediation effect will indicate an INSPIRE-mediator-PEG score pathway.

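### The planned mediation model cannot be estimated for engagement and app satisfaction, and for stigma, isolation and trust a same-visit association does not establish a pathway to PEG

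*Protocol article*

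**What the plan says.** All references are to the protocol article.

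- **Mediators and common factors** lists the variables: "Secondary mediators (i.e., variables that indirectly exert influence on outcomes) include stigma and isolation, trust in healthcare, engagement, and satisfaction with the INSPIRE intervention".
- **Trial design** makes them an aim. Secondary analyses are to determine whether "secondary mediators of stigma and isolation, trust in healthcare, and satisfaction with the INSPIRE intervention play a role in improved pain outcomes". Engagement is absent from that sentence.
- **Study measures** defines adherence with the intervention by "app usage data including module completion rates and log in times, and attendance for coaching sessions".
- **Table 1** gives the schedule. Social isolation, internalized stigma and healthcare trust are marked at baseline and 12 months; adherence/engagement at 3 and 12 months; the Mobile App Rating Scale at 3 months only. The four primary mediators are marked at baseline, 3, 6 and 12 months.
- **Waitlist control condition** gives controls a manual and one orientation visit. They have no coach, and they are offered the app only after completing the 12 months.
- **Causal mediation analysis** specifies two models, both with adjustment for covariates from baseline. The first step is "a generalized linear model will be fitted for mediators at follow-ups as the outcome and the intervention (INSPIRE vs. control) as the predictor". The second step reads: "another linear model will be fitted for the outcome PEG reduction over 12 months on the intervention (INSPIRE), mediators, and intervention*mediator interactions". The reading of the result is fixed in advance: "A significant mediation effect will indicate an INSPIRE-mediator-PEG score pathway". No mediator is exempted.

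**The concern.** The two-model approach needs a mediator that can vary in both arms and that comes before the outcome it is meant to explain. Two of the listed variables fail the first condition, because they describe use of, or opinion about, something that only the INSPIRE arm receives. Three meet the first condition but have no follow-up value earlier than the final visit.

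Examining mediators is a stated aim. For engagement and app satisfaction, software may drop a redundant term without comment and print a number that depends on which term was dropped. For stigma, isolation and trust, a significant result would be declared a pathway even if lower pain had produced the change in the mediator.

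**Working it through.** The article gives no figure on this point to reproduce. The check uses the Table 1 schedule, the control-arm content and the form of the outcome model.

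**1. Which instrument is satisfaction?** The mediator section cites references 92–95, and Table 1 attaches 95 to the Mobile App Rating Scale. The Global Impression of Change, which the article calls global satisfaction with treatment, is a secondary outcome with its own reference (86). Satisfaction as a mediator is therefore an app rating.

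**2. Engagement and app rating.** Write A for arm (1 = INSPIRE) and M for the mediator. The outcome model has four columns: 1, A, M, A×M.

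- *Controls scored zero.* M = 0 whenever A = 0, so A×M = M in every row. Two columns are identical and the rank is 3 of 4. The slope in the INSPIRE arm can be estimated; the slope in controls, and hence the interaction, cannot.
- *Controls missing.* Only INSPIRE rows remain, so A = 1 throughout. Then A equals the intercept and A×M equals M. The rank is 2 of 4.

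A numerical rank check gave the same results. More participants or more covariates do not help. If the interaction is dropped and controls are scored zero, the model can be fitted, but the indirect effect is then the within-INSPIRE slope times mean INSPIRE engagement. That is a self-selected dose-response. For the app rating, zero has no meaning as a score.

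**3. Stigma, isolation and trust.** These are measured in both arms. The four columns have rank 4 of 4 and baseline values are available as covariates, so the model can be fitted. The difficulty is order in time:

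| | Baseline | 3 mo | 6 mo | 12 mo |
|---|---|---|---|---|
| PEG | X | X | X | X |
| Stigma, isolation, trust | X | – | – | X |

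The only post-randomisation mediator value is taken at the visit that closes the 12-month PEG outcome. It also cannot explain the 3-month primary effect, which it follows by nine months.

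**4. What reverse causation could do (illustration; all coefficients are assumed).** Let B be a baseline common cause with variance 1, and M0 the baseline mediator. Set:

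- 12-month PEG: Y = 0.5·B − 0.3·A + error (SD 0.8)
- 12-month mediator: M = 0.5·M0 + 0.4·Y + error (SD 0.6)

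PEG drives the mediator and the mediator has no effect on PEG, so the true indirect effect is 0. Adjusting for M0 and B:

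- Effect of arm on the mediator: 0.4 × (−0.3) = −0.12
- Apparent slope of PEG on the mediator: (0.4 × 0.8²) / (0.4² × 0.8² + 0.6²) = 0.256 / 0.4624 = 0.554
- Apparent indirect effect: −0.12 × 0.554 = −0.066
- Share of total: 0.066 / 0.30 = 22%

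A simulation of 200,000 participants, fitting the model with the interaction, gave −0.068 of a total of −0.301, or about 23%; the difference from 22% is simulation error. Using PEG reduction as the outcome reverses signs and leaves the share unchanged.

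**The case against.** **It is not certain that engagement and app satisfaction enter this model.** The mediation section speaks only of mediators. The abstract says that secondary mediators may include these variables, the trial design section omits engagement, the pathway figure is not shown, and an analysis plan could allocate mediators to models. The plan also already has a potential-outcome analysis for nonadherence. This narrows the point without removing it: the article labels both variables mediators, describes one mediation model and exempts nothing from it. Satisfaction also appears in the trial design aim.

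**A reader might infer that the model identifies no secondary mediator at all.** The documents do not support that. Stigma, isolation and trust have baseline and 12-month values in both arms and the model has full rank. What they lack is evidence of order, so a causal reading needs an added assumption that the mediator changed before PEG did.

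**A reader might also infer that the primary mediators, measured at 3 and 6 months, are sound by contrast.** That does not follow either. The text says only that mediators at follow-ups are used and does not fix the visit, so a 12-month value could be taken and would have the same weakness. Even a 3-month value shares its visit with 3-month PEG, and no mediator is randomised.

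**Mediation is a secondary analysis.** This stands, and it limits the weight of the point.

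**Conclusion.** The point holds in two parts of different strength.

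- **Engagement and app satisfaction (two of five secondary mediators):** the stated outcome model cannot be estimated. This rests on controls having neither app nor coach before month 12, which the article states, and on satisfaction meaning the Mobile App Rating Scale, which the reference numbers indicate.
- **Stigma, isolation and trust (three of five):** the model can be fitted, but a significant indirect effect does not establish a pathway, because reverse causation is not excluded. The 23% shows that the artefact can be material under assumed coefficients; it does not estimate the bias in this trial.

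The primary intention-to-treat comparison at 3 months and the sample size are untouched. The plan should be changed because a stated aim is tied to a decision rule that these data cannot support.

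**What to change.** 1. Remove engagement and app satisfaction from the mediation model. Handle engagement through the nonadherence analysis already planned as item (3) of the secondary analyses of the primary outcome. Report the app rating descriptively within the INSPIRE arm, and label any within-arm dose-response as non-randomised.
2. Report stigma, isolation and trust as treatment effects at 12 months and as associations with PEG at that visit.
3. Restrict the pathway sentence to mediators measured before the PEG outcome they are meant to explain. For the primary mediators, pair the 3-month mediator with later PEG, adjusted for baseline mediator and baseline PEG.
4. State that any such result is conditional on no unmeasured mediator-outcome confounding. Do not add 3-month PEG as an ordinary covariate: it is measured after randomisation, is expected to respond to treatment, and is the primary outcome.

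The cost is wording in the protocol and analysis plan, with no new data. Recruitment is due to end around April 2026, so 12-month follow-up runs to about April 2027 and the change can precede the final analysis. The downside is fewer mediation claims.

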### Procedures to optimize INSPIRE intervention fidelity and participant adherence

#### Intervention fidelity

##### Mobile App Content

The INSPIRE app was developed and validated by CBT, MBI, MFI, and general pain management experts who were part of the INSPIRE research team [118]. App content was further reviewed and approved by the INSPIRE Clinical Science and Practice Advisory Board to further assess and improve intervention fidelity.

##### Pain Management Coaching

Pain coaches completed 80 hours of training about the INSPIRE intervention including coaching strategies such as motivational interviewing using didactics and mock coaching sessions with experts and peers. Coach competence was measured by expert evaluations of 4 recorded mock coaching sessions (weeks 1, 4, 5, and 6) using a standardized rubric. Those coaches not passing completed remediation by reviewing the sessions, applying the rubric themselves to their and other coaches’ sessions, and continuing practice until attaining a passing score of 80% utilizing the standardized rubric. During the study, 5% of coaching sessions will be randomly selected (via randomization generator) to record and review by intervention experts using a standardized rubric for additional and ongoing fidelity and quality assurance.

#### Participant retention, adherence, and engagement

Given the challenges often faced by our target population and the limitations caused by chronic pain, substantial attention and support will be provided to maximize participant retention and completion of survey instruments at all time points. Text, email, and/or phone call reminders from CRCs will be used to remind participants of assessments and to provide the relevant survey link to REDCap. Non-adherence will be addressed by coaches within the telehealth sessions to better understand and address obstacles to survey completion.

In accordance with Good Clinical Practice (GCP) and International Council for Harmonisation (ICH) guidelines, all participants retain the right to withdraw from the clinical trial at any point. Discontinuation from trial intervention does not mean discontinuation of the study altogether, and the remaining study procedures, follow-up assessment/visits, and data collection will be completed as indicated in the protocol (unless consent is specifically withdrawn).

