### Blinding

Study personnel responsible for survey administration and/or data analysis will be blind to participant condition and are not unblinded. Participants will not be blinded as it was not possible to create a “sham” digital intervention and coaching program.

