#### INSPIRE intervention: health coaches

This innovative intervention element will include a one-hour orientation/introduction to the program followed by 12 weekly telehealth coaching calls to patients guided by PRO scores and module completion data summarized in the coach’s dashboard. One-hour booster sessions will be delivered at months 5 and 11. The exact roles and expectations of the coaches were determined by current best practices of multiculturally validated programs, patient preferences, and provider/clinic/system needs, with all duties and procedures summarized in a detailed coaching manual [74, 109–115]. We anticipate one PhD-level clinician will serve as the lead coach that supervises 4–5 additional coaches using the UCSF coaching model with a digital patient registry and online dashboard to track participant progress [116].

Coaches will utilize a manual to standardize content facilitation for each week’s materials. Coaches take notes, help patients establish goals, follow their progress, and problem solve issues around intervention engagement and adherence. Coaches were trained for over 80 hours using didactics, role plays, and video review with feedback and remediation when necessary. Coaches will direct participants to their PCP regarding medications, referrals to specialty care, and to address urgent medical issues, and will report AE’s to the study PI and coordinator.

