### Sample size justification

The sample size calculation was based on the primary analysis comparing the primary outcome (PEG scores) between the INSPIRE and control groups at 3 months. Based on the literature, we expect to observe an effect size of 0.3 in PEG score at 3 months [57, 58, 60, 70, 119, 120]. With a power of 0.8 and Type I error of 0.05 in a two-sided independent t-test, assuming 73% retention, a sample size of 586 (293/group) is needed at the enrollment to identify such an effect size at 3 months.

Although we will use Holm’s step-down procedure to adjust for multiple comparisons in secondary analyses, we will take a conservative approach in the power calculation for secondary analyses using Bonferroni with an individual Type I error of 0.01 to control for the family-wise Type I error in 5 comparisons on secondary outcomes. The sample size of 586 (293/group) at the enrollment will provide a power of 0.8 to detect an effect size of 0.366 (a group difference of 0.366*SD) in secondary outcomes between the INSPIRE and control groups. We consider the detectable effect sizes realistic that we expect to observe in the study. With a less conservative Holm’s step-down approach than Bonferroni that we will use in actual secondary analyses to adjust for multiple comparisons, the planned sample size will detect a smaller effect size than 0.366 with a power of 0.80 for secondary outcomes. Adverse events, severe adverse events, and unanticipated problems during the study will be summarized with frequencies and percentages and compared between the treatment groups using Fisher’s exact test or Chi-squared test as appropriate.

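### Coaches, who exist only in the INSPIRE arm, work on survey completion and report adverse events, so follow-up effort and adverse event capture can differ by arm

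*Protocol article*

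**What the plan says.** All references are to the protocol article.

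- **Coach contact.** Coaching is part of the INSPIRE intervention (INSPIRE intervention: mobile app; INSPIRE intervention: health coaches): one orientation, 12 weekly calls, and boosters at months 5 and 11. Controls receive the manual and one orientation visit, and have no coach (Study onboarding; Waitlist control condition).
- **Survey completion.** Participant retention, adherence, and engagement has coordinators send reminders by text, email or phone, with no restriction to one arm. It then adds: "Non-adherence will be addressed by coaches within the telehealth sessions to better understand and address obstacles to survey completion".
- **Adverse event reporting.** The health coaches section says that coaches "will report AE’s to the study PI and coordinator". The section on reporting of adverse events and the oversight section cover review and onward reporting. They do not say how events are elicited from participants. Table 1 has no adverse event assessment in either arm.
- **Adverse event analysis.** Sample size justification states: "Adverse events, severe adverse events, and unanticipated problems during the study will be summarized with frequencies and percentages and compared between the treatment groups". The tests it names are Fisher's exact and chi-squared.
- **Blinding.** "Study personnel responsible for survey administration and/or data analysis will be blind to participant condition and are not unblinded". Participants are not blinded.

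**The concern.** Two kinds of data are gathered with more effort in one arm than in the other, and the difference in effort comes from the treatment itself.

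For adverse events, a staff member with a reporting duty speaks to INSPIRE participants nearly every week for three months. The article describes no counterpart for controls. A significance test on events gathered this way compares closeness of observation as well as safety. The likely direction is against INSPIRE, because more of its events would be heard about.

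For the primary outcome, the coaching weeks lead up to the 3-month PEG survey. In an unblinded trial with a self-reported outcome, extra help with survey completion in one arm could change who responds in that arm. What is at stake is the missing-at-random basis of the linear mixed model, not power.

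**Working it through.** **Contacts.** INSPIRE: 1 orientation + 12 weekly calls + 2 boosters = 15 coach contacts. Control: 0 coach contacts and 1 orientation visit. Coordinator reminders are additional and not limited to one arm.

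**Figures taken from the plan.** The article gives no retention by arm and no adverse event rate. It gives a common rate: "assuming 73% retention, a sample size of 586 (293/group) is needed at the enrollment". That enrolment figure does not follow from its stated inputs. An effect of 0.3, two-sided 5% and 80% power need 176 per group by t-test, and 176/0.73 gives 242 per group, not 293; 60% retention would give 176/0.60 = 294. This is a separate inconsistency. Only 293 per arm and an average retention of 73% are used below, and the point does not depend on how they were obtained.

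**Adverse event test.** Let p be the true proportion with an event, equal in both arms, and let c1 and c0 be the shares captured in the INSPIRE and control arms. The test sees p·c1 and p·c0. Every p and c is an assumption. The entries are the probability that a two-sided Fisher's exact test at 5% rejects, by exact enumeration with 293 per arm.

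| True incidence p | Capture 90% vs 70% | Capture 80% vs 40% |
|---|---|---|
| 20% | observed 18% vs 14%: 0.23 | observed 16% vs 8%: 0.83 |
| 10% | observed 9% vs 7%: 0.11 | observed 8% vs 4%: 0.46 |
| 5% | observed 4.5% vs 3.5%: 0.06 | observed 4% vs 2%: 0.22 |
| 2% | observed 1.8% vs 1.4%: 0.03 | observed 1.6% vs 0.8%: 0.06 |

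With equal capture (80% in both arms) the same test rejects in 0.035 and 0.038 of trials at 10% and 20% incidence. At those incidences, nearly all rejections under unequal capture point to more events on INSPIRE.

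**Retention and PEG.** Suppose non-responders differ from responders by D in both arms, and none of D is explained by observed data. A responder-based contrast then shifts by D × (r1 − r0), where r1 and r0 are the retention proportions. Assume r1 = 0.78 and r0 = 0.68 (mean 0.73) and D = 0.5 SD:

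- Shift: 0.5 × 0.10 = 0.05 SD, and 0.05/0.3 = 17% of the target effect.
- Standard error: √(1/228.5 + 1/199.2) = 0.097 SD, so the two-sided type I error becomes 0.081.
- With D = 0.3 SD the shift is 0.03 SD and the type I error 0.061.
- Power for 0.3 is 0.872, against 0.873 with equal retention, so power is practically unchanged.

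The sign is not known in advance. With higher retention on INSPIRE, worse-off non-responders make INSPIRE look worse and better-off ones make it look better.

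**When the shift reaches the mixed model.** Group and the time-by-group interaction are in the model, and all available PEG scores are used. Missingness that depends only on arm and observed scores is missing at random and gives no bias. The 0.05 SD is therefore the figure when the whole of D remains unexplained by those data.

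**The case against.** The strongest case on the other side has four parts.

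1. **Retention may not differ at all.** Coordinator reminders are not restricted to one arm, and payment is tied to completing each assessment (Recruitment). A reader might infer that retention will differ and will bias the PEG comparison. The article supports only a risk. Even a real gap does not by itself bias the planned model, and Secondary analyses of the primary outcome plans dropout covariates, multiple imputation or pattern mixture models. Timing helps too: the weekly sessions end about when the 3-month survey falls due, and the next coach contact is at month 5. Coaches can encourage completion beforehand but have little chance to pursue a missed primary survey. All of this stands.
2. **Blinding is not contradicted.** A reader might infer that coaches, who cannot be blind, administer surveys in breach of the Blinding section. The text has them deal with obstacles to completion. It does not say that they administer, read or score a survey. This stands.
3. **A symmetric adverse event query may exist elsewhere.** The article condenses a full protocol and cites an approved data and safety monitoring plan. A reader might infer that harms in controls go unseen, but the missing row in Table 1 does not prove it, and review and reporting apply to the whole trial. This limits the claim. It does not remove the stated facts that one arm has an extra reporting channel and that the test, as worded, is not confined to events collected the same way in both arms.
4. **The adverse event figures depend on invented rates.** Capture of 80% against 40% is an extreme case, and at 2% incidence even that gap hardly matters. The article itself regards the risk of serious events as minimal. The range, not its upper end, is the result.

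**Conclusion.** The point holds as a risk built into the procedures. Coaches are in one arm only, help with survey completion, and report adverse events that are then tested between arms.

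The adverse event test is the main problem, with probable detection bias against INSPIRE. Its size rests on assumed capture and incidence: false significance in about 11% to 23% of trials for a moderate capture gap at 10% to 20% incidence, about 46% to 83% for an extreme gap, and little effect for rare events. The planned dropout analyses do not address it.

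Differential missingness in PEG is the lesser problem. It needs missingness that depends on unobserved PEG given arm and observed scores. It amounts to at most 0.05 SD under an assumed 10-point retention gap and a wholly unexplained 0.5 SD difference, equal in both arms. The documents do not establish that retention will differ, that blinding is breached, or that control-arm harms go unrecorded. The change is worth making because it is cheap.

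**What to change.** - Take survey completion out of the coach's role. Leave it solely to the coordinators, on one identical schedule of reminders and non-responder calls in both arms.
- Ask one identical adverse event question in the 3-, 6- and 12-month surveys in both arms. If the full protocol already has a symmetric query, state it.
- Restrict the between-arm test to those answers. List coach-reported events descriptively, with a note that no such channel exists for controls.
- Report retention by arm at each time point.

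Cost: a wording change, one short survey item, and possibly a slightly lower response in the INSPIRE arm without coach encouragement. Recruitment is stated to run from April 2025 to about April 2026, so 12-month surveys continue to about April 2027. Participants who have already passed a time point would lack the item there, but if it is introduced on the same date in both arms the comparison stays symmetric.
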